## Abstract

**Background:**

Peanut allergy is an increasingly common health problem. Current treatment guidelines are based on strict avoidance. However, in the last few years, oral immunotherapy protocols have shown promising results yielding increased tolerance to peanut in allergic children. Adolescence is particularly at risk.

**Methods/Design:**

We have designed a randomized, double-blind, placebo-controlled, multicenter study to investigate the efficacy and safety of peanut oral escalating immunotherapy in a 12- to 18–year-old population with proved allergy to peanut. Patients are selected when the threshold of peanut intake is over 100 mg and 2 cumulated g on the first double-blind, placebo-controlled oral food challenge (DBPCOFC).

During the build-up placebo-controlled blinded phase, doses containing peanut or placebo will be administered by gradual up-dosing from 10 mg to 2 g with 2-weekly increments. After this first randomized phase, the desensitized participants will continue to intake native peanut in an unblinded process during 13 or 37 weeks following a second randomization. Adverse events are picked up and managed throughout the entire protocol.

The main endpoint is the percentage of patients with negative DBPCOFC at the threshold of 2 g of cumulative peanut at the end of the build-up phase of 24 weeks.

Secondary endpoints include: (1) desensitization 6 weeks and 6 months after the end of the maintenance phase; (2) adverse effects during the build-up phase; (3) immunological profile confirming peanut desensitization. Immunologic assays will be carried out at every DBPCOFC and at the middle of the build-up phase to evaluate the peanut immunologic profile modifications.

**Discussion:**

This double-blind, placebo-controlled study will be, to our knowledge, the first evaluation of a peanut oral immunotherapy protocol in teenagers in the purpose to reduce severe reactions after unexpected intake and to improve quality of life.

**Trial registration:**

ClinicalTrial.gov: NCT02046083 (23 January 2014).

## Background

Peanut allergy is one of the most common forms of food allergy encountered in clinical pediatric practice especially in children above 3 years old. It affects about 1% to 2% of children in France [1]. The allergy carries a risk of acute life-threatening reactions even after the ingestion of small amounts of peanut [2]. Peanut allergy spontaneously resolves in about 20% of children only [3] and thus current guidelines for allergy management consist of strict avoidance of the allergen. Such a diet is challenging for children and their families because of the widespread presence of peanut in food preparations. Hence, in a study of Swedish children, despite theoretical strict avoidance, peanut was reported to be responsible for 19% of anaphylaxis reactions [4]. Anaphylaxis can be life-threatening and this risk justifies the holding of rescue medications such as self-injectable epinephrine at home and at school. Adolescents are particularly at risk because they have a high incidence of severe reactions following unwitting ingestion of peanut [5]. These reactions account for most of the fatalities caused by food-induced anaphylaxis [6]. However, adolescent behavior is unpredictable and can include consumption of alcohol, which makes it difficult to adhere to a strict avoidance diet. Several studies have indicated that early consumption of allergenic food like peanuts may be a more beneficial strategy. For example, in Israel, where infants are introduced early to peanuts, the prevalence of peanut allergy is lower in children than in the UK [7]. In adolescent populations, specific oral immunotherapy is an interesting way of modifying the natural history of peanut allergy. Since 2009, peanut-specific oral immunotherapy protocols have been implemented with the aim of inducing desensitization, which was achieved in 61% [8] to 84% of cases [9]. In a Cochrane review published in 2012 by Sheikh and Nurmatov [10], only one double-blind, placebo-controlled study [9] validated the concept of oral immunotherapy for peanut allergy in children. However, this trial involved only children aged less than 10 years, and nothing is known about desensitization in adolescents with high-level peanut specific IgE. Recently, Anagnostou *et al*. demonstrated the interest of tolerance induction versus strict avoidance [11].

Our aim was to assess the efficacy and safety of oral immunotherapy in a teenage population at risk of severe reactions to peanut in order to improve their quality of life and enable them to eat freely in any restaurant and in the school canteen. We also decided to investigate the length of the maintenance phase needed to induce long-term desensitization.

## Methods/Design

### Objectives and design

The main objective is to investigate in an adolescent population the efficacy and safety of peanut oral escalating immunotherapy up to a maximum level of 2 g of peanut. The secondary objectives are to compare two maintenance durations (13 and 37 weeks) with 2 g daily of peanut intake, to investigate the immunologic effects of peanut oral immunotherapy, and to assess the safety of the procedure.

The study was designed in two phases: build-up and maintenance immunotherapy (Figure 1). After a baseline double-blind placebo-controlled oral food challenge (DBPCOFC), participants will be randomized (R1) in the build-up phase (24 weeks) to one of the two groups (treatment or placebo). At the end of the build-up phase, desensitized participants will be randomized (R2) for the maintenance phase (13 versus 37 weeks’ duration). During this second phase there will be no blinding.

**Figure 1 Fig1:**
[figure not shown]
Study design. Children aged 12 to 18 years with peanut allergy proven in a first double-blind placebo-controlled oral food challenge (DBPCOFC) will enter a double-blind placebo-controlled induction phase through a first 2:1 randomization (R1). After a successful build-up phase, the maintenance phase duration will be determined by a second 1:1 randomization (R2). Double arrow: DBPCOFC. (dotted area: 24 weeks normal dietary; shaded area : 6 weeks wash-out).

A subsequent DBPCOFC will be performed 6 weeks and 6 months after the completion of the maintenance phase to evaluate the peanut’s tolerance after stopping the daily peanut’s consumption. The participants will have a normal diet (trace of peanut and small quantities of peanut) after the penultimate DBPCOFC.

### Consent statement

This peanut oral immunotherapy study is a randomized, double-blind, placebo-controlled, multicenter trial. It was approved by the Institutional Review Board of the University Hospital of Clermont-Ferrand (France). By 1 March 2013, the study had been approved for all centers by a central ethics committee (Comité de Protection des Personnes Sud-Est VI, Clermont-Ferrand, France) with the registration number RBHP-2013-[name] and registered at http://www.clinicaltrials.gov (NCT02046083). Before inclusion the patients (and their parents) are fully informed of the aims, procedures, safety measures, and practical aspects of the protocol. A written consent is mandatory before inclusion to confirm their agreement.

### Study population

#### Inclusion criteria

Adolescents aged 12 to 18 years with a clinical history of reaction to peanut within 60 min of ingestion or a positive DBPCOFC to peanut below 2 cumulated g will be included.

Sensitization is proved by a positive skin prick test (SPT) (3 mm over the negative control) and/or a serum specific IgE level over 12 IU/mL for peanut or over 5.8 IU/mL for Ara h2 recombinant fraction to peanut.

#### Exclusion criteria

Patients with a history of severe peanut anaphylaxis requiring hospitalization in an intensive care unit, participants with severe persistent asthma or poorly controlled atopic dermatitis, or those with another concomitant severe food allergy (egg, milk, nuts, and so on) will be excluded, as will patients affected by lactose intolerance or sunflower allergy.

Participants who tolerate more than 2 cumulated g of peanut during the initial DBPCFC or those with an allergic reaction occurring below an intake of 100 cumulated mg peanut will not be included. Patients unable to follow a daily intake of capsules or to fill in a daily recording of clinical signs were not included as well as those living more far from a reference center to assume management of an acute reaction within 15 min, and those attending another clinical trial. The occurrence of a severe adverse event will lead to exclusion by the investigator or the expert committee.

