### Procedures and interventions

Adolescents will be recruited from the pediatric allergy unit in the University Hospital, Clermont-Ferrand, France and from the pediatric departments of Saint-Etienne and Lyon hospitals.

In an education session, the patients and their parents will learn how to recognize food allergy symptoms, to evaluate their severity, and to use the rescue medications and self-injectable epinephrine.

A first DBPCOFC is managed according to national recommendations [12]. It consists in the intake of incremental doses of peanut or placebo according to a randomized plan. A food challenge is declared positive as soon as an objective reaction occurs. At this time discontinuation and management of the clinical reaction should be considered [13]. Blind is released after the second day of challenge. Patients with a peanut allergy threshold above 100 mg and below 2 g cumulative intake of peanut are included in the build-up phase.

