### Judgment criterion

During each DBPCFC, peanut intake will be incremented every 30 min as follows: 10 mg, 20 mg, 40 mg, 80 mg, 160 mg, 300 mg, 500 mg, 890 mg, 2 g, 5 g. DBPCOFC will be considered positive at the threshold of 2 g if a patient exhibits at least one clinical objective sign of allergic reaction (dermatological, respiratory, gastrointestinal, or systemic involvement) within 30 min following the intake. If the patient reports subjective signs, 30 min can be added. Thereafter, the cumulative intake dose will be considered as the positive threshold of the OFC.

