### Study endpoints

The main endpoint is the percentage of patients who satisfy to the judgement criterion, that is, negative DBPCOFC at the threshold of 2 g of cumulative intake of peanut at the end of the build-up phase of 24 weeks.

Secondary endpoints include:the percentage of patients with a negative DBPCOFC at the threshold of 2 cumulated g performed 6 weeks and 6 months after the end of the maintenance phase;the percentage of patients who quadruplet their reaction threshold between the first and the second DBPCOFC;the percentage of adolescents who have adverse effects during the build-up phase (degree and number of adverse events, use of rescue medication, rescue consultations; and hospitalizations);immunological profile confirming peanut desensitization (skin prick tests, peanut specific IgE and IgG 4, basophil activation test).

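### The challenge doses reach exactly 2 g at the 890 mg step, and the eligibility texts disagree at that value, which is also the primary-endpoint cut-off

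*Protocol article*

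**What the plan says.** The protocol article sets the upper limit for entry in several places, in different terms.

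- **Inclusion criteria:** adolescents "with a clinical history of reaction to peanut within 60 min of ingestion or a positive DBPCOFC to peanut below 2 cumulated g". The two routes are joined by an *or*, and the history route carries no dose limit.
- **Exclusion criteria:** not to be included are "Participants who tolerate more than 2 cumulated g of peanut during the initial DBPCFC". This limit concerns the dose tolerated.
- **Procedures and interventions:** "Patients with a peanut allergy threshold above 100 mg and below 2 g cumulative intake of peanut are included". This limit concerns the dose at reaction.
- **Abstract, Methods/Design:** the selection sentence puts the threshold over 100 mg and then names 2 g without saying on which side of it the patient must lie.

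The Judgment criterion section gives the challenge steps as "10 mg, 20 mg, 40 mg, 80 mg, 160 mg, 300 mg, 500 mg, 890 mg, 2 g, 5 g" and defines a positive result by "the cumulative intake dose will be considered as the positive threshold of the OFC". The primary endpoint in Study endpoints is a "negative DBPCOFC at the threshold of 2 g of cumulative intake of peanut at the end of the build-up phase of 24 weeks".

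**The concern.** The same 2 g value decides who enters and who counts as a success. The two uses should complement each other: a patient who would be a success on the baseline challenge should not be randomised. If the dose ladder jumped over 2 g, it would not matter whether a rule said *more than*, *below* or *at* 2 g. The ladder does not jump over it, so the choice of word decides the fate of two kinds of patient.

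A baseline passer who entered and kept that tolerance would be a success in either arm whatever the treatment did. That raises both rates and shrinks the contrast. The patient would also go forward as desensitised to the second randomisation. Three centres applying one eligibility section without the others could classify the same challenge result differently.

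**Working it through.** **1. Where 2 g falls on the ladder.** Running sum of the steps in Judgment criterion:

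10 + 20 + 40 + 80 + 160 + 300 + 500 + 890 = 2,000 mg.

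The full series is 10, 30, 70, 150, 310, 610, 1,110, 2,000, 4,000 and 9,000 mg. The 2 g cut-off is therefore reproduced exactly, at the 890 mg step. The lower limit causes no such trouble, because the sums go from 70 to 150 mg and never equal 100 mg.

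**2. Each first-reaction step under each rule.** Tolerated dose is the sum before the reacting step. Threshold is the sum including it.

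| Reacts at step | Tolerated (mg) | Threshold (mg) | Challenge arm of Inclusion criteria (below 2 g) | Exclusion criteria | Procedures and interventions | Endpoint met at baseline |
|---|---|---|---|---|---|---|
| 10, 20 or 40 mg | 0 to 30 | 10 to 70 | yes | excluded | not included | no |
| 80, 160, 300 or 500 mg | 70 to 610 | 150 to 1,110 | yes | not excluded | included | no |
| 890 mg | 1,110 | 2,000 | no | **not excluded** | **not included** | no |
| 2 g | 2,000 | 4,000 | no | **not excluded** | **not included** | **yes** |
| 5 g | 4,000 | 9,000 | no | excluded | not included | yes |
| none | 9,000 | none | no | excluded | not included | yes |

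The texts disagree on two rows.

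- *Reactor at the 2 g step.* 2,000 is not more than 2,000, so the Exclusion criteria let this patient through. On this ladder the next tolerated dose is 4,000 mg, so that criterion bites only from 4 g. The history arm of the Inclusion criteria admits the patient, given a reaction history and proven sensitisation. The threshold of 4,000 mg is not below 2,000, so Procedures and interventions does not. The secondary endpoint of a fourfold rise in threshold is also out of reach: 4 × 4,000 = 16,000 mg, against a ladder that ends at 9,000 mg.
- *Reactor at the 890 mg step.* The challenge is positive at 2 g, so the patient fails the endpoint at baseline. The threshold of exactly 2,000 mg is not below 2 g. This is one of the five reaction steps above 100 mg (150, 310, 610, 1,110 and 2,000 mg). That is a count of steps, not of patients.

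**3. Size if baseline passers were randomised.** Inputs from Statistics and Randomizations: 60 patients at 2:1, hence 40 versus 20; rates of 60% and 10%; Fisher's exact test at two-sided 0.05; stated power 90%. The documents give no share of baseline passers. Let *s* be an assumed share, equal in both arms, all of whom pass again after build-up:

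- active rate = 0.60(1 − s) + s
- placebo rate = 0.10(1 − s) + s
- difference = 0.50(1 − s)

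Power is the exact probability, summed over all outcomes of two binomials (40 and 20), that Fisher's p is below 0.05.

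| s (assumed) | Active | Placebo | Difference (points) | Exact Fisher power |
|---|---|---|---|---|
| 0 | 60% | 10% | 50 | 97.8% |
| 5% | 62% | 14.5% | 47.5 | 94.6% |
| 10% | 64% | 19% | 45 | 90.0% |
| 20% | 68% | 28% | 40 | 79.3% |
| 30% | 72% | 37% | 35 | 70.0% |

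Power starts above the stated 90%, which is why there is room before it falls below.

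**The case against.** The strongest reply is that eligibility rules apply together, and a patient who is not excluded is not thereby admitted. Taken together, the Inclusion criteria, Exclusion criteria and Procedures and interventions give one answer: both borderline patients stay out, because the last of these requires a threshold below 2 g. This stands. A reader might infer from the Exclusion criteria that patients who already pass the endpoint will be randomised. The documents do not support that, since it would take a centre that ignored Procedures and interventions and relied on the history arm.

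A reader might likewise infer from the *or* that history alone leads to randomisation. It does not: every candidate has a baseline challenge first, the dose limits in the Exclusion criteria refer to that challenge, and Figure 1 requires allergy proven by it. The *or* is loose wording that should be tightened.

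Nor do the figures show a loss of power. The shares are assumed, and the dilution falls on both arms, so it weakens the contrast and does not create a false one.

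The reply does not remove the contradiction. The article states its entry limit in four places, the versions differ at a value that the ladder hits, and the abstract cannot settle the matter. This is a conflict between stated rules, not detail left to a fuller document.

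**Conclusion.** The eligibility text is wrong as written at exactly 2 g. For two of the ten reaction steps (890 mg and 2 g) the Exclusion criteria and Procedures and interventions give different answers. In one of the two, the patient is already a success on the primary endpoint. The conclusion rests on the listed doses and on reading the threshold as the cumulative dose at reaction, as Judgment criterion defines it.

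The practical effect depends on an unknown share of patients. Only if the Inclusion and Exclusion criteria were used without Procedures and interventions could baseline passers be randomised. On the assumption that they remain passers, exact Fisher power at 40 versus 20 stays at or above the stated 90% up to a share of about 10%, and is 79.3% at 20%. The point is worth correcting because the value defines both entry and success, not because the trial is likely to be underpowered.

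**What to change.** - Use one upper-bound rule in the Abstract, Inclusion criteria, Exclusion criteria and Procedures and interventions, worded as the complement of the primary endpoint: anyone who completes the 2 g cumulative step without an objective reaction at baseline is not randomised. In the Exclusion criteria this means tolerating 2 g or more, in place of more than 2 g.
- State once whether a patient who reacts at the 890 mg step is eligible. Such a patient fails the endpoint at baseline, so either answer is compatible with it; the choice is the sponsor's.
- In the Inclusion criteria, say that a qualifying positive baseline challenge is required and that history alone is not enough, in line with Figure 1 and Procedures and interventions. Simply turning the *or* into an *and* would go too far: it would make a reaction history mandatory, which nothing in the documents calls for.

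The cost is a wording amendment. At most, patients at the 890 mg and 2 g steps are classified differently. Because recruitment opened in September 2013, the baseline thresholds of patients already randomised should be checked for values of 2 g and 4 g.

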### Randomizations

After the initial DBPCOFC, attribution of active treatment (peanut) or placebo will be done by a first randomization (R1) at a ratio treatment/placebo of 2:1. Stratification will be performed every six participants. For the second randomization (R2), the ratio between the two groups will be set at 1:1. Randomizations will be stratified by location due to the multisite nature of the study.

Each patient will be identified by an identification number consisting of the number of permanent investigation center and an individual patient number. The patient number will be assigned chronologically on the randomization list. A comprehensive document describing the randomization procedure will be kept as confidential at the Children Clinical Research Centre, INSERM CIC 1405.

### Procedures and interventions

Adolescents will be recruited from the pediatric allergy unit in the University Hospital, Clermont-Ferrand, France and from the pediatric departments of Saint-Etienne and Lyon hospitals.

In an education session, the patients and their parents will learn how to recognize food allergy symptoms, to evaluate their severity, and to use the rescue medications and self-injectable epinephrine.

A first DBPCOFC is managed according to national recommendations [12]. It consists in the intake of incremental doses of peanut or placebo according to a randomized plan. A food challenge is declared positive as soon as an objective reaction occurs. At this time discontinuation and management of the clinical reaction should be considered [13]. Blind is released after the second day of challenge. Patients with a peanut allergy threshold above 100 mg and below 2 g cumulative intake of peanut are included in the build-up phase.

During the build-up phase, doses will be administered by gradual up-dosing from 10 mg to 2 g of peanut with 2-weekly increments. Experimental treatment will consist in administration of doses of either peanut or placebo provided by the pharmacy department. The raw material of the peanut treatment is a mixture of peanuts (95.7%) and sunflower oil (4.3%), supplied by MENGUYS ©. A certificate of alimentary confirmed the food as suitable for human diet. The doses contain 10 mg to 500 mg of peanut. Placebo will be similarly prepared and comprise the same raw material except for the peanut paste. The participants should take the treatment in the morning. Practice of any sport is prohibited for 2 h. During the protocol, adverse events and rescue medications are picked up in the patient’s paper diary. They are quoted according to Ring and Messmer classification [13]. In the event of a grade 1 reaction occurring during the build-up phase, the increments process will not be modified. If a grade 2 or 3 without anaphylaxis reaction occurs, the level of peanut intake may be maintained for three additional periods of 2 weeks, that is, for a maximum duration of 8 weeks. In all cases symptomatic drugs will be prescribed, depending on the severity of the reaction, H1 antihistamines in cases of a mild reaction (urticaria, rhinitis, conjunctivitis, oral syndrome, acute abdominal pain, and so on), inhaled betamimetics in cases of bronchospasm, and systemic steroids and epinephrine in cases of grade 3 or 4 reaction (systemic anaphylaxis, anaphylactic shock). In the event of a grade 3 adverse reaction without anaphylactic shock, disruption should be considered. Grade 3 with anaphylactic shock and grade 4 reactions should lead to questioning the independent committee and excluding the patient. During the entire protocol, the patients are allowed to take any medication including inhaled steroids and antihistamines if needed.

During the maintenance phase, children will receive a 2 g package of crushed peanut of the same origin. Clinical follow-up is performed in the investigation center every 4 weeks. A third DBPCOFC is performed 6 weeks after the end of this maintenance phase of 13 versus 37 weeks’ duration, depending on second randomization. Finally, a fourth DBPCOFC is performed after a 6-month period where diet is free, peanut intake is freely recommended. During the entire protocol, participants will follow a diet consisting of avoidance of peanut. A weekly meeting involving all investigators allows defining the management of adverse events and the protocol’s achievements. Discontinuation of the protocol can be decided at any time by the investigator or the patient, and is mandatory when ordered by the independent data monitoring safety committee.

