Adverse events will be recorded and managed. If serious unexpected events occur, the independent security committee will decide on whether to suspend the protocol. The mechanisms involved in desensitization and tolerance induction will be investigated.

During the build-up and maintenance phases, patients will be asked to retain a strict avoidance of peanut. However, certain co-morbidity factors could interfere with the evolution of peanut allergy under peanut induction of tolerance, in particular associated food allergies, quality of control of asthma, and infectious concomitant diseases. There will be a 6-month follow-up period after the end of the protocol during which the patients will remain under observation in the outpatient clinic. We shall compare the two duration periods of the maintenance phase in our protocol with those of previous publications. The behavior of patients who are scheduled to return to a non-restricted diet is also an unknown factor. All patients will be invited to go on eating daily reasonable amounts of peanut. One cannot expect that all patients will behave similarly in terms of daily diet. DBPCOFC 4 will feed this debate.

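### Peanut intake is recommended after the third challenge with no condition on its result, so patients who have just had a non-severe reaction at or below 2 g cumulative are included unless the investigator intervenes

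*Protocol article*

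**What the plan says.** Three places in the protocol article describe diet after the third challenge.

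- Procedures and interventions: "a fourth DBPCOFC is performed after a 6-month period where diet is free, peanut intake is freely recommended".
- Objectives and design, in the text with Figure 1: "The participants will have a normal diet (trace of peanut and small quantities of peanut) after the penultimate DBPCOFC".
- Discussion: "All patients will be invited to go on eating daily reasonable amounts of peanut".

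Study endpoints lists as a secondary endpoint the "percentage of patients with a negative DBPCOFC at the threshold of 2 cumulated g performed 6 weeks and 6 months after the end" of maintenance. The Judgment criterion section calls a challenge positive at 2 g when at least one objective allergic sign appears.

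Two sentences bear on avoidance. Procedures and interventions, directly after the free-diet sentence, asks for peanut avoidance throughout the protocol. The Discussion is narrower: "During the build-up and maintenance phases, patients will be asked to retain a strict avoidance of peanut".

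On stopping a patient, Exclusion criteria says "The occurrence of a severe adverse event will lead to exclusion by the investigator or the expert committee". Procedures and interventions excludes patients after grade 3 reactions with anaphylactic shock and after grade 4 reactions, asks that interruption be considered for grade 3 without shock, and lets the investigator or the patient stop at any time. Suspension of protocol allows individual suspension for a severe adverse event, or where build-up cannot be completed.

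**The concern.** The third challenge comes after a six-week wash-out and tests whether tolerance persists without daily intake. Some patients will react. For them the challenge gives fresh evidence of allergy at a measured dose, yet the advice that follows is the same as for patients who tolerated the full amount.

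At stake is a foreseeable reaction outside the clinic, in an age group that the Background section describes as particularly at risk. Training in symptom recognition and self-injectable epinephrine, and the Discussion's provision that "the patients will remain under observation in the outpatient clinic", reduce the harm of a reaction. They do not prevent it.

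**Working it through.** No stated sample size, power or alpha figure is at issue, so there is none to reproduce. The check is a reading of the rules, followed by a rough scale.

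**1. Is the advice conditional?** The three diet statements refer to the participants, to all patients, or to the period as a whole. None mentions the third-challenge result. In practice they cover everyone who reaches that challenge, that is, those desensitized at the end of build-up and entered at the second randomization.

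**2. Does a nearby sentence supply the condition?**
- The Discussion remarks that "The behavior of patients who are scheduled to return to a non-restricted diet is also an unknown factor". This does not say who is scheduled for that diet and who is not, so it defines no subgroup.
- The avoidance sentence in Procedures and interventions, read literally, contradicts the free-diet sentence just before it. The Discussion limits strict avoidance to build-up and maintenance, so it restores no restriction for reactors.

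**3. Do the stopping rules cover reactors?**

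| Third-challenge reaction | Rule that applies |
|---|---|
| Severe adverse event; grade 3 with shock; grade 4 | Exclusion, possible suspension, committee involvement |
| Grade 3 without shock | Interruption to be considered (discretionary; stated among the build-up rules) |
| Other non-severe objective reaction | General investigator discretion and the weekly investigators' meeting only |

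**4. Do the words on amount protect reactors?** The challenge steps in Judgment criterion add up as follows: 10, 30, 70, 150, 310, 610, 1,110 and 2,000 mg, since 10 + 20 + 40 + 80 + 160 + 300 + 500 + 890 = 2,000. A patient positive at or below 2 g may therefore have a threshold anywhere from 10 mg to 2,000 mg cumulative. Amounts described only as small or reasonable are not tied to that threshold. Entry to the trial, by contrast, is refused to anyone reacting below 100 mg cumulative.

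**5. Scale.** Inputs are 60 patients randomized 2:1 (Statistics; Randomizations) and planning success rates of 60% and 10% (Statistics).
- Treated: 60 × 2/3 = 40. Placebo: 60 × 1/3 = 20.
- Expected at the second randomization: 0.60 × 40 + 0.10 × 20 = 24 + 2 = 26. Statistics plans for 40.
- The article gives no rate of positive third challenges, so 10% to 50% is assumed.
- With 26 patients: 0.10 × 26 = 2.6 (about 3) to 0.50 × 26 = 13.
- With 40 patients: 0.10 × 40 = 4 to 0.50 × 40 = 20.

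These counts include any severe reactors, who fall under the exclusion rules. Within the assumed range they are upper values for the non-severe group.

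**The case against.** The best defence is that this is an absence, not an error. A journal article condenses a longer protocol, and what to tell an individual who fails a late challenge could be left to that document. The broadest wording sits in the Discussion, among remarks on how unpredictable diet will be, and an invitation to eat reasonable amounts leaves room for individual advice. The patients have already been desensitized and assigned 2 g daily for 13 or 37 weeks, are trained in rescue treatment, and are followed in clinic.

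Part of this stands. The amounts are tempered, discretion exists, and the call to consider interruption for grade 3 without shock narrows the group left without a specific rule. But the article does more than stay silent: it positively recommends intake, in the procedures as well as the Discussion, and addresses it to everyone. If the full protocol contains a condition, the article misstates it and still needs correcting.

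A reader might also infer that reactors are told they may eat up to 2 g. The documents do not support that. The 2 g figure in the Discussion explains the choice of tolerance threshold and is not tied to these six months. Moreover, a cumulative challenge dose reached over eight steps, the largest 890 mg, is not a dietary portion.

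**Conclusion.** The point holds as a limited safety gap. The stated rule advises peanut intake to every patient who reaches the third challenge, and so includes those with a non-severe objective reaction at or below 2 g cumulative, unless an investigator intervenes by discretion. It rests on reading the three diet statements as written and on the absence of any condition elsewhere in the article.

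The number affected is unknown; the 3 to 13, or 4 to 20, depend wholly on the assumed 10% to 50%. Two wider readings should be resisted. The plan does not send severe reactors home to eat peanut, because the rules on severe events apply. Nor does the gap undermine the comparison of 13 and 37 weeks of maintenance, since the same advice is given in both arms.

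**What to change.** In Objectives and design (the text with Figure 1), Procedures and interventions, and the Discussion, limit the free-intake recommendation to patients with a negative third challenge at 2 g cumulative. State that patients with a positive result return to avoidance, or to an investigator-set amount below their reaction threshold, have the fourth challenge where safe, and remain in the intention-to-treat denominator of the second randomization.

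Also limit the avoidance sentence in Procedures and interventions to build-up and maintenance, as the Discussion does, so that it no longer contradicts the free diet. The six-week wash-out in Figure 1 should then keep its own explicit instruction.

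The cost is wording and no new data, but the change is not purely editorial. Diet in the last six months would depend on the third-challenge result, so the six-month success percentage may be somewhat lower. It must be described as the result under that rule, not under free intake for all.
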